**5.3 Statistical Analysis**

This protocol follows an open-label, non-randomised design. This study is exploratory in nature. All statistical analyses will be performed with descriptive and exploratory purposes and the results of statistical tests with confidence intervals, when given, will thus be considered an aid to evaluate the reliability of the observed result. The data will be summarised with respect to demographic and baseline characteristics, efficacy, observation and measurements, safety observations and measurements.

The primary outcomes analysed will be change in the resting and 24-hour ambulatory blood pressure, and the 2-hour glucose on OGTT. Secondary endpoints will be analysed in a similar fashion.

*Sample size*

This is a pilot study and no formal statistical analysis or power calculations will be performed. The number of patients has been selected to see if there is any trend in effect, and to assess the tolerability of the intervention. The information gathered will inform the design of a larger study, likely double-blind placebo controlled.

**5.4 Outcome measures**

***Primary end points*** will be the difference at 8 weeks, compared to baseline, in systolic blood pressure (BP) (resting and ambulatory) and 2-hour glucose tolerance during a 75g oral glucose tolerance test. BP will be measured in the sitting position, left arm taken twice, separated by 5 mins, after 10 mins resting (according to British Hypertension Society, UK [BHS] guidelines). 24-hour ambulatory blood pressure will be measured using standard BHS-approved monitors.

The primary endpoints have been chosen, as they are associated with important clinical outcomes. Baseline 24 hour ambulatory BP monitoring will be performed in the week starting treatment between the first visit (screening) and second visit (treatment start) and again at weeks 4 and 8. The daytime and nocturnal BP as determined by 24-hour ambulatory monitoring will be assessed independently and together to take account of the influence of the circadian rhythm in serum cortisol. The baseline glucose tolerance test will be performed on the first day of treatment (treatment start) before the first dose and again at weeks 4 and 8.

***Secondary end points*** will be compared to baseline: 1) the difference in BP and Glucose tolerance at 4 weeks; 2) homeostasis model assessment of insulin resistance (HOMA-IR) 42, and the insulin Sensitivity Index (ISI) 43 at 4 and 8 weeks, as calculated from oral glucose tolerance test: insulin and glucose at -15, 0, 30, 60 and 120 minutes, with oral glucose 75g at time 0 (except for those on insulin therapy, whose investigation will be limited to basal and 120 minute plasma glucose); 3) the difference in the mean plasma 0900h plasma ACTH, and salivary 0900 and 2400h cortisol values at 4 and 8 weeks; 4) the difference in fasting lipids at 8 weeks; 5) the difference in bone turnover markers at 8 weeks; 6) difference in urinary steroid profile at week 8; 7) the difference between depression, quality of life and fatigue questionnaires at 4 and 8 weeks. Tertiary endpoint will be any major cardiovascular adverse events at 8 weeks. Other biochemical safety parameters are summarized in the table above.

We considered other means of assessing glucose homeostasis, such as clamp studies, but felt that these would be too onerous for the participants and, importantly, not directly translatable to routine clinical practice. We accept that HOMA-IR is often quoted as being most appropriate for large epidemiological studies, but the correlation with euglycaemic clamp studies is high, and it has the advantage of simplicity and generalisability to clinical practice. Similarly the correlation between clamp studies and ISI is high.

The level of morning plasma ACTH and salivary nocturnal cortisol are anticipated to increase under the action of the study drug and give a biological marker for the effect of blockade. The repeated measurement will give greater confidence in the observation of drug activity. Salivary cortisol is stable at room temperature and thus can be collected by patients at home and brought or sent to the CRF. Similarly, assessment of the urinary steroid profile will be determined to assess the effects of mifepristone and the influence of increased circulating ACTH. Excess cortisol will suppress serum osteocalcin, a marker of bone formation, and thus the predicted effect of mifepristone would be an increase in this marker, and give insight as to the effect on bone health.

Clinically overt Cushing’s syndrome is associated with impairments in health-related subjective health status, that does not fully return to normal for many years after treatment 44. In SCS it is not established if quality of life is impaired. In view of this and the potential effects of altering excess cortisol on mood and general well-being, three validated questionnaires will be used to assess the effects of mifepristone therapy on health-related subjective health status. In addition to assessing any changes induced by mifepristone therapy the scores will be compared to sex and age–matched controls drawn from questionnaire-specific reference cohorts (available at the University of Sheffield), to establish if these parameters are impaired in SCS.

**5.5 Setting**

The Clinical Research Facility (CRF), Royal Hallamshire Hospital, Sheffield Teaching Hospitals Foundation Trust and University of Sheffield

**5.6 Participants**

Participants will be recruited from a group of patients who have attended the endocrine unit at the Sheffield Teaching Hospitals Foundation Trust and have already had clinical and biochemical evaluation for adrenal incidentalomas and been found to have evidence of SCS without the clinical phenotype of Cushing’s syndrome. Sheffield Teaching Hospitals Foundation Trust has one of the largest endocrine units in the UK, with six endocrinologists and a specialised laparoscopic adrenal surgeon, and receives direct referrals from a population catchment area of 3 million. All patients identified with an adrenal incidentaloma on CT/MRI are referred for assessment under a single protocol through this single point of referral, greatly facilitating recruitment.

**5.7 Recruitment**

We currently have 50 patients who fulfil the entry criteria, with a referral rate of 5-6 new patients per month. Therefore, there should be no issues over recruitment.

**5.8 Intervention**

Treatment will be in the form of an oral tablet of oral mifepristone twice-daily 200mg (0900h and 2100h) one hour before food, for eight weeks. Patients will attend the CRF at 0900h fasted at weekly intervals from weeks 0-4, and then again at weeks 6 and 8. A major advantage to this study design, compared to performing adrenalectomy, is that the treatment is immediately reversible, is not associated with the inherent risks of surgery, and it will inform design of a larger study, and tell whether an invasive approach by adrenal surgery is justified for study in this common patient group.

**5.9 Instruments**

Validated Health related quality of life scores (HRQOL) will be used as defined in section 5.4

A). *Depression* will be measured by Beck Depression Inventory ® (BDI®-II). The BDI-II takes approximately 10 minutes to complete. Each item has one numerical answer ranging from 0 (low depression) to 3 (maximum depression). Thus the total score ranges from 0 to 63.

B). *Quality of life* will be measured by the Short Form (SF-36), a 36-item health survey questionnaire to record general well-being during the previous 30 days and overall evaluation of health. Scores are expressed on a 0-100 scale, and higher scores are associated with a better quality of life.

C). *Fatigue* will be measured by Multidimensional Fatigue Index (MFI-20). This is a 5-point scale that comprises 20 statements to assess fatigue. Scores vary from 0-20, a high score indicating higher experienced fatigue.

**5.10 Project plan**

*Timelines***.** After regulatory and ethical approval it is anticipated that recruitment will be rapid and the study complete within 4-6 months. MHRA approval will be required. Mifepristone is already licensed for use in early pregnancy. MHRA regulatory approval was recently sought and granted to HRA Pharma for a multi-centre international study of the use of mifepristone in severe Cushing’s syndrome due to ectopic ACTH secretion. It is, therefore, anticipated that regulatory approval will be granted for this study.

Proposed timelines:

MHRA submission: in progress

Ethical submission: March 2008

Project Start date: November 2008

Last patient visit: May 2009

Database Lock: February 2009

Data analysis and write up March 2009

*Communication*

This is a pilot study and thus will not provide a definitive answer. Nevertheless, research findings will be disseminated by presentation at National and International meetings in both Endocrine and Cardiovascular areas, and by scientific publication, as and when appropriate. Engagement with the media will be facilitated by [name]’s close working relationship with the UK Society for Endocrinology and US Endocrine Society, and their respective patient representation. [name] is a trustee of UK-based patient charities.

Data Storage

Data will be collected and retained in accordance with the Data Protection Act 1998. The site file containing data will be available to the study staff and secured in a locked area on the CRF, RHH.

**6.0 Project management**

The investigator and independent physician will meet at least monthly to ensure that the project is progressing in a timely fashion (for ethical and governance issues see section 8).

**7.0 Expertise of the researcher and associated team**

The applicants involved have all the expertise necessary for such a trial. [name] has a major interest in the assessment and treatment of glucocorticoid excess, a detailed knowledge of the biology, and experience of clinical trials in this area, and sees many patients with this condition as part of a dedicated diagnostic clinical protocol, and has many publications in the area of glucocorticoids. [name] is an Academic Clinical Fellow and will gain invaluable experience in clinical research and be responsible for the day to day running of the study under the supervision of [name].

The clinical work will take place on the dedicated Clinical Research Facility (CRF) in Sheffield, which is jointly run by the University of Sheffield and The Sheffield Teaching Hospitals Foundation Trust. All of the facilities for performing the trial are available on the CRF including all necessary sample storage facilities.

**8.0 Ethical issues**

The study will be approved by the appropriate NHD Research Ethics Committees prior to commencement of the study. The study will be performed in accordance to the Declaration of Helsinki, ICH guidelines covering Good Clinical (research) Practice and the European Clinical Trials Directive and NHS Research Governance. A steering committee will be created according to GCP guidance. [name] (Sheffield) has already agreed to undertake this. Any adverse event will be flagged. An adverse event (AE) can be any unfavourable and unintended sign (including an abnormal laboratory finding), symptom, or disease temporally associated with the use of a medicinal product, whether or not considered related to the medicinal product.

If depression questionnaire highlights a level of depression requiring medical or psychiatric intervention necessary action will be taken by research team members.

Previous data suggests that mifepristone is well tolerated when taken for long periods of time (months to years). The main concern is the potential for inducing adrenal insufficiency.

*Safety and well-being of study participants*

Patients will be monitored for the non-specific symptoms and signs of relative adrenal insufficiency. It is unlikely that there will be any unanticipated side effects, but any potential adverse event will be recorded according to GCP guidelines and standard definitions.

#### *Interruption or discontinuation of treatment*

The term discontinuation refers to a patient’s non-compliance in the study. In this study, information about the discontinuation will be collected during the study. If in the opinion of the investigator, patients are considered to be treatment failures (i.e. require immediate alternative medical therapy) they will be discontinued from this study and the end of study evaluations will be completed.

Patients who discontinue the study prematurely must complete the final safety evaluations at the time of the discontinuation of their study. The study completion forms must be completed for all patients with an explanation of why the patient was withdrawn from the study, even if the patient refused to return for the final visits. Patients who discontinue prematurely due to their significant adverse events should continue to be followed until the resolution of the adverse event(s), and the relevant sections of the CRF should be completed as appropriate. Patients who discontinue due to clinically significant abnormalities in clinical laboratory results should continue to be evaluated until no abnormality results or is judged to be permanent.

It will be documented whether or not each patient completed the clinical study. If there are any patients participating in the study, and whose treatment or observations have been discontinued, the reason will be recorded. Reasons that a patient may discontinue participation are considered to constitute one of the following:

1. Adverse event(s)
2. Abnormal laboratory values
3. Abnormal test procedures
4. Unsatisfactory therapeutic effect
5. Subject’s condition no longer requires study treatment
6. Protocol violation
7. Subject withdrew consent
8. Lost to follow up
9. Administrative problems
10. Death

#### *Treatments and Blinding*

This is an open-label non-randomised study. Blinding is therefore not applicable.

*Concomitant therapy*

All medications taken during the four weeks prior to visit two will be recorded. Patients will be discouraged from taking any medication during the study that has not been taken at baseline. An exception is the medication that was required to treat an adverse event. Patients will not take any new prescription or over-the-counter medication during the study unless the Investigator has given their prior consent. Paracetamol is an acceptable concomitant medication, and if necessary, will be prescribed by a Physician. If any medication, is required, the name, strength, frequency of dosing, and reason for its use will be documented in the patient's Case Report Form. As mifepristone is metabolised by the CYP 3A4 enzyme system concomitant use of enzyme inhibitors or enzyme inducers may raise or reduce levels of mifepristone respectively. Mifepristone being an enzyme inhibitor of CYP 3A4 may lead to an increase in serum levels of drugs that are CYP 3A4 substrates. This factor should be taken into consideration if any of these drugs are taken.

*Contraception*

All male patients, including those who have been vasectomised, will be asked to use barrier contraception (e.g condom + spermicide) if they are sexually active with premenopausal women, throughout the whole trial and for a period of seven days after the last dose. This is to ensure there is no inadvertent transfer of mifepristone to a fetus in the semen.

Further, male patients and premenopausal partners should use two highly effective methods of contraception for three months from the last dose of mifepristone. This is to allow the passage of one spermatogenic cycle of 60-70 days after treatment has stopped before stopping contraceptive measures.

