**5.2 Design**

This is an open labelled, pilot study over eight weeks at one centre: We feel that given the lack of widespread experience of using the anti-glucocorticoid actions of the drug in man in general, and the lack of data entirely for this indication, that the detailed nature of investigation is justified. As a compromise, the first 5 intervention visits are weekly, and the next two 2-weekly. A screening visit (week -4; visit 1) will also take place up to 4 weeks prior to the first intervention visit (week 0; Visit 2). A follow up visit will take place 72 hours after the last dose. We will recruit 6 individuals with SCS. The overall study design and assessments is shown below, including assessments made for secondary endpoints: Intervention - Mifepristone 200mg BD from week 0-8.

| **Week** | **-4** | **0** | **1** | **2** | **3** | **4** | **6** | **8** | **8** |
| --- | --- | --- | --- | --- | --- | --- | --- | --- | --- |
| Visit | 1 | 2 | 3 | 4 | 5 | 6 | 7 | 8 | 9 |
| Informed Consent |  |  |  |  |  |  |  |  |  |
| Treatment (sc: screening; s: Treatment start; e: Treatment end; fu: Follow up 72 hours after last dose) | Nsc | Ys | Y | Y | Y | Y | Y | Ye | Nfu |
| Resting BP and clinical assessment |  |  |  |  |  |  |  |  |  |
| 24-hour BP (during week of study) |  |  |  |  |  |  |  |  |  |
| OGTT – 0,15,30,60,90,120 mins samples for insulin and glucose |  |  |  |  |  |  |  |  |  |
| U+E |  |  |  |  |  |  |  |  |  |
| LFT |  |  |  |  |  |  |  |  |  |
| TSH |  |  |  |  |  |  |  |  |  |
| FBC |  |  |  |  |  |  |  |  |  |
| Fasting lipids |  |  |  |  |  |  |  |  |  |
| 0900h/2400h salivary cortisol |  |  |  |  |  |  |  |  |  |
| 0900h serum cortisol |  |  |  |  |  |  |  |  |  |
| Plasma ACTH |  |  |  |  |  |  |  |  |  |
| Bone turnover markers – formation, serum osteocalcin; resorption, urine NTX |  |  |  |  |  |  |  |  |  |
| Urinary steroid profile (during week of study) |  |  |  |  |  |  |  |  |  |
| Health-related quality of life questionnaires |  |  |  |  |  |  |  |  |  |

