***Drug administration and compliance****:* A check on the blister packs of the tablets issued and therapeutic drug monitoring will be performed at each visit to assess and encourage compliance. All existing medication will be left unaltered for the duration of the study. The first dose of the drug (Treatment start) will be given at Visit 2 (week 0) after baseline tests have been performed. The last dose (Treatment end) will be taken in the morning at Visit 8 (week 8). The drug will be administered 1 hour before food to maximise bioavailability as mifepristone is absorbed rapidly.

***Safety****:* Clinical assessment by BP, P, temperature, weight and questioning for fatigue, headache, anorexia, nausea, arthralgia, myalgia, and abdominal pain (potential glucocorticoid deficiency, a predictable effect of mifepristone based on its known action) will be made at each study visit. Clinical experience is, however, that even total adrenal insufficiency is well tolerated in the absence of physical or infective stressors. For safety purposes each patient will also be issued with written instructions which will tell them what to do if this side effect occurs and with a supply of two dexamethasone 1mg tablets (sufficient to overcome the effects of mifepristone 400mg by taking dexamethasone 1mg/day for 2 days) to be taken on the advice of the investigators if significant symptoms are reported. In such circumstances any study subject will be asked to attend the CRF either that day or the next working day, and data entered into the CRF accordingly, and the subject asked to stop the mifepristone and withdrawn. Other uncommon but documented side effects of mifepristone used at this dose and for this time period include: skin rash (maculopapular), increased eosinophil count, joint pain, hypokalaemia. When used for >3-6 months duration endometrial hyperplasia, uterine fibroma, and endometriosis are described.

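### The two-method contraception rule is dated only from the last dose, so read literally the 8 dosing weeks carry only the barrier rule (minor safety wording)

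*Protocol*

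**What the plan says.** The Contraception paragraph of protocol section 8.0 (under Treatments and Blinding) sets two rules.

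- **Barrier rule.** All male patients, vasectomised men included, use barrier contraception "if they are sexually active with premenopausal women, throughout the whole trial and for a period of seven days after the last dose". Condom with spermicide is the example. The stated purpose is drug transfer: "This is to ensure there is no inadvertent transfer of mifepristone to a fetus in the semen".
- **Two-method rule.** The next sentence adds that "male patients and premenopausal partners should use two highly effective methods of contraception for three months from the last dose of mifepristone". The stated purpose is to let pass "one spermatogenic cycle of 60-70 days after treatment has stopped before stopping contraceptive measures".

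Section 5.2 dates the treatment. On the start it says "The first dose of the drug (Treatment start) will be given at Visit 2 (week 0) after baseline tests have been performed", and it places the last dose on the morning of Visit 8, week 8. Women are eligible only if postmenopausal, so both rules concern male patients and their partners.

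**The concern.** The two-method rule has a stated length and one stated anchor, the last dose. Taken at its word, the stricter standard begins when treatment stops, and the weeks on drug are left to the barrier rule.

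That order does not fit the rule's own reason. If sperm formed while the man is taking mifepristone are the worry, the worry begins soon after the first dose. A conception in week 4 or week 7 involves such sperm just as a conception in the weeks after dosing does. The protocol asks for two highly effective methods in the second case, does not ask for them in the first, and does not explain the difference.

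At stake is a clear safety instruction for a small group: which contraceptive standard a male patient and his premenopausal partner should follow while he is on drug.

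**Working it through.** No sample-size, power or error-rate figure bears on this point. The check sets the time windows of the two rules side by side and compares each with its stated reason.

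**Inputs**
- First dose at week 0 and last dose at week 8 (section 5.2).
- Barrier rule: whole trial plus 7 days after the last dose (section 8.0, Contraception).
- Two-method rule: three months from the last dose (same paragraph).
- Spermatogenic cycle: 60 to 70 days (same paragraph).
- Assumption: three months is taken as about 90 days.

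**Windows, counted from the first dose as day 0**
- Dosing: 8 × 7 = 56 days, so day 0 to day 56.
- Barrier rule: the whole dosing period, ending at 56 + 7 = day 63.
- Two-method rule, literal reading: day 56 to 56 + 90 = about day 146.

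**Coverage, literal reading**
- Dosing days under the two-method rule: 0 of 56.
- Dosing days under the barrier rule: 56 of 56.
- Share of the span from first dose to three months after the last dose without the two-method rule: 56/146 = 38%.
- The two rules overlap from day 56 to day 63. The second is therefore an addition to the first and does not simply replace it.

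**Is the end date consistent with its reason?** Yes. Three months exceeds the cycle by 90 − 70 = 20 to 90 − 60 = 30 days. Only the start is in question.

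**Is the start consistent with its reason?** No. The reason is that sperm which developed during treatment remain for one cycle. Sperm present on any day after the first dose have also developed partly during treatment. Nothing in the reason singles out the period after the last dose.

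**Does another section supply an earlier start?** None of the visible text does. Section 5.2 and the remaining safety text in section 8.0 set no other contraception rule for male patients.

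**The case against.** The best reply is that couples are protected during dosing and that the sentence was meant to fix an end date. Barrier contraception is mandatory throughout, even after vasectomy, and the example pairs a condom with a spermicide. It prevents conception whatever reason is given for it. The two-method sentence is introduced as an addition to the rule before it, and its rationale speaks of stopping measures after a cycle has passed, which makes sense only if they are already in use. On that reading three months after the last dose is when precautions end.

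Most of this stands. It shows that a deliberate gap is unlikely. It does not supply the missing start. The protocol sets the two rules separately, gives them different purposes, and nowhere says that condom with spermicide meets the two-method standard.

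A reader might infer more than the documents support:

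- **That dosing is unprotected.** It is not. The barrier rule covers every dosing day and the seven days after.
- **That the sponsor chose a lower standard during treatment.** The wording of the rationale points the other way.
- **That a man who stops early would be left without arrangements.** Under Safety in section 5.2, a patient who reports significant symptoms attends the research facility on the same day or the following working day, with "the subject asked to stop the mifepristone and withdrawn". Section 8.0, under interruption or discontinuation, requires final safety evaluations at that time. The team can also explain at Visit 2 what will apply once dosing ends.
- **That the short follow-up makes matters worse.** The last scheduled visit is 72 hours after the last dose, so most of the three months falls after it. Moving the start of the rule leaves those days unchanged, so this does not support the point.
- **That a risk to a fetus can be sized.** The documents give no data on harm through the male partner, and counting days of sperm development under drug would not supply any.

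**Conclusion.** The point holds as a minor error of safety wording. As written, two highly effective methods are required for about 90 days after the last dose and on none of the 56 dosing days, when the barrier rule alone applies, although the stated reason covers both periods. Continuous use was probably intended.

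The reach is small: only men with premenopausal partners, among six planned patients. No endpoint, analysis or eligibility rule is affected.

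The conclusion rests on the protocol wording alone. Consent pages were removed from the text supplied and the patient instructions are not visible. Either may already give the earlier start, in which case only the protocol sentence needs correcting. The day counts take three months as about 90 days.

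**What to change.** Reword the sentence so that male patients with premenopausal partners use two highly effective methods from the first dose (Visit 2, week 0) until three months after the last dose, whether that dose is the scheduled one or an early stop. State that this is in addition to the barrier rule, which stays as it is, and leave the three-month end date alone.

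Check that the patient instructions give the same dates, and amend them if they do not.

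The cost is one sentence in the protocol and possibly one in the patient material. The downside is a somewhat heavier contraceptive burden for the couples concerned during the 8 weeks of dosing.
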